#### Qualitative analysis

In keeping with process evaluation guidance from the Medical Research Council (MRC) [43], the process evaluation of this feasibility study will focus upon facilitators and barriers to implementation of the intervention in order to inform implementation of the intervention within a future definitive trial. It will also evaluate the acceptability and feasibility of the trial process itself to inform the conduct of a future definitive trial. Within these, following the framework recommended in the MRC guidance, we will consider the impact of context (how external factors may have influenced the delivery and functioning of the intervention, and here also the trial process) and implementation (evaluation of the way in which the intervention is delivered, and the quality and quantity of the intervention delivered, including fidelity, dose and reach).

In addition we will tentatively explore potential mechanisms of impact (how the intervention might bring about its effects, in interaction with the participants) qualitatively, to refine our current working logic model. Finally, and related to implementation, we will gather preliminary data on the long-term feasibility of this intervention within the NHS [44] through feedback gathered from referrers and therapists.

Qualitative interviews will be analysed using a framework approach [45], whereby data will be coded according to both theme and case, and then abstraction of themes and explanatory inferences will occur iteratively with codes, themes and inferences being quality-checked by a second team member.

### Data management and storage

Information in the form of routine clinical notes, measures and therapy recordings will be stored according to standard practice within the NHS service hosting the intervention. Hard copies of information/measures gathered as part of this research study will be anonymised and stored in a locked filing cabinet in a locked office in the Department of Psychology, University of Exeter, or the Spectrum Centre, University of Lancaster. Hard copies of data collected during assessments at the second study site may be stored temporarily and securely on NHS Trust premises before being transferred to Lancaster University. Consent forms will be stored separately from data, and data will be anonymised wherever possible. Data will be double-entered on a secure, web-based system maintained by the Clinical Trials Unit, University of Exeter.

The datasets generated during and/or analysed during the current study will be stored in a non-publicly available repository within the University of Exeter following completion of the trial. Anonymised data may be accessed and analysed by members of the project team and with researchers collaborating with members of the project team on the analysis of these data. With the exception of anonymised quotes from research interviews, consent from participants was not sought for sharing raw data publicly. Therefore, external researchers seeking to access the data for use in future projects must do so via request to the chief investigator (or her delegate), and projects using the data must have been approved in accordance with contemporary UK ethical and regulatory processes pertaining to the release of anonymised data under these circumstances.

Original research records will be retained for 7 years, after which they will be retained in electronic form and original records destroyed, including records of participant names and contact details, and audio files of semi-structured interviews (which will be retained only in transcribed form). The electronic records will be kept for 20 years after the end of the study. Published material will not contain patient-identifiable information.

### Study approvals

The conduct of the trial will be in accordance with the Helsinki declaration. The study has received approval from the UK National Research Ethics Service and the Health Research Authority (IRAS ID 219816) and from all relevant local approval bodies.

### Anticipated risks and benefits

Because of the inclusion of a comparison arm in which participants receive TAU, participants will have only a 50% chance of receiving the ThrIVe-B programme. Participants will be fully informed of this aspect of the trial and the reasons for it. No aspect of standard care will be withheld as a result of trial participation. Through participating in this trial, participants will receive an enhanced level of monitoring by the research team, and where suicidal risk or significant worsening of their mental state is detected, they will be directed to appropriate care, in accordance with established protocols in the relevant research centres and clinical services.

The study seeks to test a novel intervention. This is an adaptation of a well-established treatment (DBT), as applied to a population that differs in some ways from the main recipient population. There are four published studies reporting pilot trials of DBT with individuals with BD (in adolescents and adults), all with favourable results [18–21]. Our approach does not differ from these in essence, but it includes some adaptations relevant to the particular subgroup question and is tailored to a UK context. In an open trial of the ThrIVe-B programme [24], there were no unexpected serious adverse reactions to the therapy.

The participant information sheets will describe possible benefits and risks of taking part. The research team will inform participants if any new information comes to light that has a bearing upon their safety as a participant in the trial.

Individuals with bipolar spectrum disorders are at increased risk of suicide compared with the general population. We will follow established clinical and research protocols for monitoring and responding to suicide risk during therapy and research contacts. The participant information sheet will inform participants of the possibility that confidentiality could be broken where serious risk to an individual is detected; wherever possible, responses to elevated risk will be made with the participant’s knowledge and agreement.

### Adverse events

All serious adverse events that are trial- or treatment-related will be recorded and immediately reported to the chief investigator and trial sponsor. If these are also classed as unexpected they will be reported to the NRES committee. We will, in line with other complex intervention studies, monitor non-serious adverse events, serious adverse events that are not trial- or treatment-related, serious deterioration, and active withdrawals from treatment. Adverse events will include any events for which the participant consulted their GP or other medical advisor or for which the participant took new or additional medication. Symptoms of BD or cyclothymic disorder themselves are not defined as adverse events. Data on any adverse events will be collected by a member of the research team at each assessment through screening of health service use; therapists will also report any adverse events reported by participants to the trial team. Instances where participants report suicidal ideation that requires information-sharing action by the research team, according to the study risk management protocol, will be counted as adverse events.

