### Randomisation, concealment of allocation, and blinding

Eligible participants will be randomised in a 1:1 ratio, with minimisation by trial site and medication status. To ensure concealment, eligible participants will be randomised via a validated password website hosted by the Exeter Clinical Trials Unit. The first ten participants will be allocated using simple randomisation, the remainder being allocated using the minimisation procedure, maintaining a stochastic element to the algorithm to allow concealment to be maintained. Following randomisation of a given participant, he or she will be informed of their allocation by an unblinded member of the research team.

Researchers conducting follow-up assessments will be blind to study arm allocation and will remind participants of the need to conceal their allocation. We will test blindness by asking researchers to indicate at follow-up which treatment they believe the participants received and analyse any correlation with outcome. We will maintain the blinding as far as possible to maintain the quality and legitimacy of the trial and its findings; however, in the unlikely event that a participant has an adverse reaction to either treatment arm, unblinding may occur. We will unblind the researchers only in exceptional circumstances when the knowledge of the treatment arm is deemed essential to the management of the patient by their GP (e.g., serious adverse events). Any unblinding that occurs will be recorded; where possible, researchers who remain blind to participant status will conduct their future follow-up assessments. All statistical analyses will be performed by a statistician using groups indicated by an anonymised code.

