### Trial governance

A trial steering committee (TSC), independent from the sponsor, has been convened, including independent members (academic and clinical) as well as the principal investigator and trial statistician, and will meet approximately five times over the life of the project. The TSC will be responsible for advising the trial team on the conduct of the study. Given the relatively small scale of the trial a separate data monitoring and ethics committee (DMEC) will not be convened. Instead the DMEC functions (reviewing data collected including adverse events and making recommendations for the future conduct of the trial) are included within the terms of reference of the TSC. For all substantive changes to the protocol approval will be sought from the sponsor and the relevant national regulatory bodies.

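### Serious adverse events go immediately to the chief investigator and sponsor only if already classed as related, so causality must be settled before either has a stated sight of the event

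*Protocol article*

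**What the plan says.** The reporting rule is in the Adverse events section: "All serious adverse events that are trial- or treatment-related will be recorded and immediately reported to the chief investigator and trial sponsor". If such an event is also unexpected, it goes to the ethics committee. A second list, which the team undertakes to monitor, contains non-serious events together with "serious adverse events that are not trial- or treatment-related, serious deterioration, and active withdrawals from treatment". No immediate report to the chief investigator or sponsor is stated for that list.

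The same section gives two ways in which events reach the trial team. The first is the assessments: "Data on any adverse events will be collected by a member of the research team at each assessment through screening of health service use". The second is the therapists, who pass on whatever events their participants mention to them.

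The section on randomisation, concealment and blinding adds that "Researchers conducting follow-up assessments will be blind to study arm allocation". It also shows that some staff do know the arm, since participants are "informed of their allocation by an unblinded member of the research team".

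Trial governance gives review of adverse events to the trial steering committee (TSC), which "will meet approximately five times over the life of the project".

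**The concern.** Under this rule, relatedness is a condition of the immediate report and not something decided after it. Someone must classify a serious event before the chief investigator or the sponsor has any stated immediate sight of it. The information available at that moment may come from a person who does not know whether the participant received the therapy.

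Three things turn on the classification: the report to the ethics committee (Adverse events), the temporary halt after an unexpected serious adverse reaction (Criteria for discontinuation), and the first continuation criterion, which the Objectives section defines by unexpected serious adverse reactions. A related event wrongly placed in the monitored list could be missed by all three. For a feasibility trial of a new therapy, in a population that the article itself describes as at increased risk of suicide, the safety criterion should not depend on an unreviewed first label.

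**Working it through.** No figure in the plan is at issue and no arithmetic applies. The check sets the sections side by side.

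1. **Order of events.** Adverse events splits serious events into related (recorded and reported at once) and not related (monitored). The split cannot be applied until relatedness has been decided, so the decision comes before the immediate report. This follows from the stated rule and does not depend on anything the article leaves out.

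2. **Who decides.** Neither Adverse events nor Criteria for discontinuation names who decides; the latter uses the passive. Nothing assigns the task to the assessors, to the therapists or to anyone else.

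3. **First intake route: assessments.** Collection is by a research team member at each assessment. Follow-up assessors are blind. The two may often be the same people, most plausibly at months 9 and 15, where Procedure requires in-person contact. At months 3 and 6 the Outcomes section has assessments by post or online, so the overlap is less clear there. This is a reasonable inference, not a statement in the text.

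4. **Second intake route: therapists.** They know the arm but see only participants allocated to the therapy. Trial interventions schedules 15 weekly groups, up to 8 individual sessions alongside them, and one booster 3 months after therapy. For control participants throughout, and for therapy participants once those contacts end, the assessment is the only routine intake route described.

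5. **What depends on the label.**
   - Ethics report: needs related and unexpected.
   - Reaction-based halt: needs an unexpected serious reaction judged directly related to the trial or the therapy.
   - First continuation criterion: needs an unexpected serious adverse reaction.

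   All three require a positive relatedness judgement.

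6. **What does not depend on it.** Criteria for discontinuation applies the same halt process if information emerges that the therapy or trial procedures are unsafe. It also allows an individual to be discontinued when the participant, therapist or research team thinks a serious reaction likely. The TSC reviews adverse events in general. These are real safeguards, but none gives the chief investigator or sponsor an immediate report of a serious event labelled unrelated.

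**The case against.** The strongest reply is that collecting an event is not judging it. A reader might infer that blind assessors decide relatedness and cannot do so, or that therapists judge harm from their own treatment. The documents support neither. Assessors collect, therapists pass events to the trial team, and no judge is named. Staff who know the allocation exist: one tells participants their arm, and Procedure has an unblinded team member conduct the month-9 interviews. Relatedness to trial procedures can be judged without knowing the arm at all. A condensed article may also properly leave the causality workflow to the full protocol.

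Most of this stands, and it limits the point. The unnamed judge is not a finding in itself, and nothing shows that events would be classed as unrelated by default.

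The reply does not remove the stated condition on reporting. The full protocol may say who judges, but the article itself says that only related serious events are reported at once. Unblinded staff could make the judgement, yet no section routes serious events to them. The unblinding provisions help little: researchers are unblinded when knowing the arm is essential to the patient's management by the GP, not to assign causality. The provision for an adverse reaction to either arm presupposes that a reaction has been recognised.

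Two tempting measures of size should also be set aside. The 1:1 allocation describes how participants are divided, not how often an event would be misclassified. Dividing the 29-month study by about five TSC meetings does not give a documented delay, because monitoring is not confined to those meetings and the halt process is not tied to them.

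**Conclusion.** The concern holds in a limited form. The plan makes immediate reporting of a serious adverse event conditional on a prior relatedness classification, and the ethics report, the reaction-based halt and the first continuation criterion depend on that classification. Misclassification at intake is a risk, not a demonstrated outcome. The documents give no rate for it, so its size cannot be put in numbers. In a trial of 48 participants serious events should be few, but one unexpected serious adverse reaction is enough to engage the halt and the first criterion, so a single wrong label could matter.

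The conclusion rests on two assumptions: that the article's rule reflects the full protocol, and that collection at assessments falls at least partly to the blind follow-up researchers. If the second is wrong, the conditional rule remains but its tension with blinding largely goes. Severity is low to moderate, and this is best treated as a cheap improvement.

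**What to change.** Change the rule in Adverse events so that every serious adverse event in either arm is reported immediately to the chief investigator and sponsor, whatever its presumed cause. Relatedness and expectedness should then be assigned by someone who knows the allocation and does not rate outcomes. Assessors and therapists would supply the facts only, so assessors' blinding is untouched. The blinding section and Criteria for discontinuation should be worded to agree on who makes the judgement and when.

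The cost is a short change of wording and a few more reports among 48 participants. No new post should be needed, since unblinded team members already exist. Recruitment had ended by the article's status statement, so the change would apply to whatever follow-up remains and to the design of a definitive trial. Serious events already in the monitored list could be classified in the same way before the first continuation criterion is assessed.

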### Trial interventions

The ThrIVe-B programme has been developed iteratively in consultation with ThrIVe-B patients and others with personal experience of BDs. It follows five key principles of DBT: (1) clearly structured treatment; (2) application of behavioural therapy; (3) emphasis on validation of emotional response; (4) dialectical stance, balancing acceptance and change; and (5) integration of mindfulness practice. Topics covered include skills for observing events, thoughts, emotions and bipolar symptoms without reacting impulsively; balancing lifestyle and activities to maximise mood stability and healthy rather than hypomanic positive mood; and skills for down-regulating emotion, problem-solving and negotiating interpersonal difficulties (which are often a consequence and a trigger of bipolar mood swings). As is standard DBT practice ThrIVe-B emphasises the importance of participants learning skills through teaching and practice, having opportunities to generalise these skills across real-world contexts, and continuing use of skills beyond treatment end. This will be achieved structurally through a combination of group meetings (15, held weekly) and up to 8 concurrent fortnightly individual sessions of up to 45 min delivered in person or by telephone.

To enhance real-life generalisation of skills, participants in the ThrIVe-B arm will be given a custom-built smartphone application (‘app’) which alerts participants to rate their mood level at random points each day (number of daily alerts determined by user). Handsets can be borrowed by participants without their own. When mood is above or below user-determined ‘high’ and ‘low’ mood thresholds, a feedback screen appears containing advice pre-entered by the user, which can include skills learned in the ThrIVe-B programme. A version of this app, with reduced functionality, will be used to monitor mood variability in real time over 7-day periods at baseline and at follow-up for all participants.

In addition there will be an optional supporters’ group meeting (midway through the series of group meetings) during which friends or relatives can attend and learn about the skills covered, enabling them to better support the participant with use of these. To support the generalisation and ongoing adoption of skills beyond the acute treatment, patients will be invited to attend a group ‘reunion’ booster session at 3 months after therapy.

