ThrIVe-B therapists will be psychological therapists with a background in either cognitive behavioural therapy or DBT. Training for the ThrIVe-B programme will be a 5-day course. Assuming participants’ consent, therapy sessions will be taped and recordings used to develop fidelity and competency measures for use in a definitive trial. Recordings will also be used to inform weekly supervision sessions during the active treatment phase. Participants will complete the Beck Depression Inventory [25] and Altman Scale for Rating Mania [26] prior to each group session, and the scores will be used to inform their care, as well as forming part of the research data collected.

Our comparison arm is ‘usual care’. This is because there is currently no gold standard psychological treatment for this client group against which to benchmark a new treatment. There are no formal data to indicate the likely content of TAU for individuals with BPMI across the United Kingdom; thus, we will record this in terms of the services received by each participant during the trial in order to characterise the variability of TAU within and between study sites, based upon responses to the resource use questionnaire. No restrictions will be placed on the content of TAU, other than the study entry criterion which excludes individuals currently receiving psychological therapy for BD.

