### Outcomes

We will conduct follow-up assessments at 3, 6, 9 and 15 months after baseline, with the 3- and 6-month assessments being conducted via post or online, and the 9- and 15-month assessments including a face-to-face or telephone interview.

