### Data analysis

#### Quantitative data analysis

Patients’ demographic characteristics at baseline will be reported by treatment group. The primary analyses will be performed after 9-month follow-up and after data cleaning is completed and the database finalised. Further analyses will be performed after the final 15-month follow-up. No interim analyses are planned.

All analyses will be done on an intention-to-treat basis; included outcomes will be reported according to randomised allocation and regardless of the treatment actually received. There will be no possibility of participants allocated to the control arm receiving the intervention; it is possible that participants allocated to the intervention will in actuality receive none of the intervention or will not complete the intervention (defined as attendance of at least 50% of group sessions). All outcomes will be reported descriptively. At 9-month follow-up only, an inferential analysis will be performed for continuous outcomes only, reporting the relevant 95% CI for the between-group mean difference (intervention minus TAU), but no *p* value. Inferential analyses will include the randomisation covariates: site and baseline medication status. No interactions between intervention status and covariates are planned.

Proportions of participants recruited (of those approached) and those lost to follow-up at 3, 6, 9 and 15 months, will be reported with 95% CIs. All analyses will use complete case data only. No attempts to address missing data, such as multiple imputation, will be made.

The economic analysis will take the NHS and social care perspective. No covariate analysis or subanalysis will be conducted, because this is a feasibility trial and is not powered for such inferential analyses. Descriptive data for each arm will be reported with CIs for between-group comparisons. No *p* values will be reported.

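### Therapist reports add an adverse event route that exists only in the ThrIVe-B arm, so by-arm counts combining both routes are expected to run higher there even with no true difference in harm

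*Protocol article*

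**What the plan says.** All locations are in the protocol article.

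- **Common route.** The Adverse events section states: "Data on any adverse events will be collected by a member of the research team at each assessment through screening of health service use". Outcomes fixes the schedule: "We will conduct follow-up assessments at 3, 6, 9 and 15 months after baseline".
- **Second route (Adverse events).** "therapists will also report any adverse events reported by participants to the trial team".
- **Who has a trial therapist (Quantitative data analysis).** "There will be no possibility of participants allocated to the control arm receiving the intervention".
- **Therapy contact (Trial interventions).** "group meetings (15, held weekly) and up to 8 concurrent fortnightly individual sessions of up to 45 min", plus an invitation to one booster session three months after therapy.
- **Symptom scales tied to therapy (Trial interventions).** "Participants will complete the Beck Depression Inventory [25] and Altman Scale for Rating Mania [26] prior to each group session". The scores guide care and also enter the research data.
- **Other monitored harms (Adverse events).** Serious deterioration and active withdrawal from treatment are tracked as well. Symptoms of the bipolar condition itself are excluded from the adverse event definition. Suicidal ideation is counted in this form: "Instances where participants report suicidal ideation that requires information-sharing action by the research team".
- **Use of the data.** Quantitative data analysis reports outcomes descriptively and by randomised allocation. Trial governance gives the trial steering committee (TSC) the task of reviewing adverse events and advising on the future conduct of the trial.

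**The concern.** The two routes do not have equal reach. Screening at assessments is the same in both arms. Therapist reporting adds detection in one arm and none in the other. If the counts are combined and shown by arm, the ThrIVe-B column includes events that would have gone unrecorded had the same person been allocated to treatment as usual (TAU).

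Serious deterioration is open to the same problem if it is identified from the depression and mania scales given before group sessions, because TAU participants do not complete them. Active withdrawal from the trial treatment can by definition occur only in ThrIVe-B.

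At stake are how the TSC reads any by-arm harms table and the harms procedure that a definitive trial would inherit. This is more than a detail left to an analysis plan. The article fixes the collection method, and the source of an event cannot be recovered reliably afterwards if it was not recorded at the time.

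**Working it through.** The plan gives no figure on this point to reproduce. The check counts planned contacts and then applies a simple detection model whose inputs are assumptions.

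**1. Planned contacts at which an event can surface**

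- Both arms: 4 follow-ups (months 3, 6, 9 and 15).
- ThrIVe-B only: 15 group + up to 8 individual = up to 23, or 24 with the booster.
- To 15 months: 4 in TAU against up to 4 + 23 = 27 in ThrIVe-B (28 with the booster).

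This shows that the routes are unequal. It does not measure detection, because each screening looks back over an interval.

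**2. Detection model**

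Let the true risk *p* be equal in both arms. Screening finds a share *s* of events in each arm. Therapists find a share *t* of what screening misses, in ThrIVe-B only.

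- Recorded risk in TAU: *p* × *s*
- Recorded risk in ThrIVe-B: *p* × [*s* + (1 − *s*) × *t*]
- Ratio: [*s* + (1 − *s*) × *t*] / *s*, which does not depend on *p*
- 95% half-width for the difference: 1.96 × √[*a*(1 − *a*)/24 + *b*(1 − *b*)/24], where *a* and *b* are the two recorded risks

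The 24 per arm comes from Sample size. The values *p* = 0.30 and all *s* and *t* are assumptions.

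Example, *s* = 0.75 and *t* = 0.5: the ratio is (0.75 + 0.25 × 0.5)/0.75 = 0.875/0.75 = 1.17. Expected participants with a recorded event are 24 × 0.30 × 0.875 = 6.3 against 24 × 0.30 × 0.75 = 5.4. The difference is 0.30 × 0.125 = 3.75 points.

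| *s* | *t* | Ratio | ThrIVe-B, of 24 | TAU, of 24 | Difference (points) | 95% half-width (points) |
|---|---|---|---|---|---|---|
| 1.00 | any | 1.00 | 7.2 | 7.2 | 0 | 25.9 |
| 0.90 | 0.30 | 1.03 | 6.7 | 6.5 | 0.90 | 25.2 |
| 0.75 | 0.30 | 1.10 | 5.9 | 5.4 | 2.25 | 24.0 |
| 0.75 | 0.50 | 1.17 | 6.3 | 5.4 | 3.75 | 24.3 |
| 0.50 | 0.50 | 1.50 | 5.4 | 3.6 | 7.50 | 22.0 |
| 0.40 | 0.75 | 2.1 | 6.1 | 2.9 | 13.50 | 21.8 |

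The direction is always towards ThrIVe-B unless *s* = 1 or *t* = 0. The difference is below the half-width in every row and small against it in all but the last.

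**3. How plausible the top of the range is**

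Weekly group therapy lasts about 15 weeks. Fifteen months is 15 × 52/12 = 65 weeks, so therapy covers 15/65 = 23% of follow-up. To month 9 (39 weeks) it covers 15/39 = 38%. If missed events were spread evenly and therapists heard only of those during therapy, *t* could not exceed these shares. With *s* = 0.50, the ratio would then be at most (0.50 + 0.50 × 0.38)/0.50 = 1.38 to month 9. The 2.1 therefore needs both poor screening and missed events concentrated in the therapy period.

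**4. After restriction to the common route**

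Detection is *s* in both arms, so the expected ratio is 1.00 under no true difference, given equal follow-up.

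**The case against.** The strongest reply has four parts.

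- **No by-arm adverse event comparison is stated.** This is correct. Reporting by allocation and TSC review make such a table likely, but the article does not announce one or say that the two routes will be combined. The point is therefore conditional on the routes being combined.
- **The common screening suits the definition.** Adverse events include those that led to medical advice or to new or additional medication. The resource use questionnaire looks back six months or to the last assessment, so its windows can span the whole follow-up. Screening may therefore find most events in both arms, which would put the ratio near 1.00. This stands, and it is why the size is left open.
- **Bipolar symptoms are not adverse events.** This also stands. The pre-session scales bear on deterioration, not on general adverse event counts.
- **Both arms have other information on mood.** Under Secondary outcome measures, relevant sections of the Structured Clinical Interview for DSM (SCID) cover affective episodes at 9 and 15 months in both arms. Under Experience sampling, TAU participants rate mood on the app from month 3 to month 9, although the article does not make those ratings a safety check.

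A reader might also infer that assessment mode disadvantages TAU, since Outcomes has "with the 3- and 6-month assessments being conducted via post or online". That mode applies to both arms, and Procedure lets participants choose another. Follow-up assessors are to be blind to allocation.

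A reader might further infer that suicidal ideation is undercounted in ThrIVe-B, because the definition refers to action by the research team. The article does not settle this. Risk is monitored in therapy as well as in research contacts, therapists report adverse events to the trial team, and the risk management protocol is not shown.

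**Conclusion.** The point holds in a limited form. Any by-arm adverse event count that combines screening with therapist reports is expected to be higher in ThrIVe-B when there is no true difference. This rests on reading the therapists in the Adverse events section as the trial's own, who have no contact with TAU participants as therapists. The size is unknown. The 1.03 to 2.1 range depends entirely on assumed detection rates, and 1.00 is reached if screening is complete. With 24 per arm, chance variation exceeds the bias in every scenario tried, but the bias is systematic and would carry over to a larger trial that copied the procedure. Deterioration is affected only if it is identified from the pre-session scales.

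Two stronger conclusions are tempting, and the article does not support them. One is that every by-arm safety comparison is distorted: a comparison restricted to the common screening is symmetric. The other is that the safety continuation criterion is compromised: under Objectives it asks whether an unexpected serious adverse reaction occurred, which is not a contrast between arms.

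**What to change.** 1. Record the source of every adverse event (assessment screening or therapist report) when it is entered.
2. Base by-arm adverse event counts, including those given to the TSC, on the assessment screening common to both arms.
3. List therapist-reported events, pre-session scale scores and treatment withdrawals separately, labelled as available in ThrIVe-B only.
4. Compare deterioration on measures that both arms complete: the nine-item Patient Health Questionnaire (PHQ-9) at all follow-ups and SCID affective episodes at 9 and 15 months.
5. Tabulate suicidal ideation needing information-sharing action by whether it arose in a research or a therapy contact.

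The cost is one field on the adverse event form and a change of table layout. The downside is that fewer events enter the by-arm comparison, although all are still reported. Therapist reporting continues as planned, and no clinical rule changes.
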